## Abstract

**Background:**

In the Lake Victoria basin of western Kenya, malaria remains highly endemic despite high coverage of interventions such as mass distribution of long-lasting insecticidal nets (LLIN), indoor residual spraying (IRS) programs, and improvement of availability and accessibility of rapid diagnostic tests (RDT) and artemisinin-based combination therapy (ACT) at community healthcare facilities. We hypothesize that one major cause of the residual transmission is the lack of motivation among residents for malaria prevention and early treatment.

**Methods:**

This study will aim to develop a demand-side policy tool to encourage local residents’ active malaria prevention and early treatment-seeking behaviors. We examine the causal impact of a financial incentive intervention complemented with malaria education to residents in malaria-prone areas. A cluster-randomized controlled trial is designed to assess the effect of the financial incentive intervention on reducing malaria prevalence in residents of Suba South in Homa Bay County, Kenya. The intervention includes two components. The first component is the introduction of a financial incentive scheme tied to negative RDT results for malaria infection among the target population. This study is an attempt to promote behavioral changes in the residents by providing them with monetary incentives. The project has two different forms of incentive schemes. One is a conditional cash transfer (CCT) that offers a small reward (200 Ksh) for non-infected subjects during the follow-up survey, and the other is a lottery incentive scheme (LIS) that gives a lottery with a 10% chance of winning a large reward (2000 Ksh) instead of the small reward. The second component is a knowledge enhancement with animated tablet-based malaria educational material (EDU) developed by the research team. It complements the incentive scheme by providing the appropriate knowledge to the residents for malaria elimination. We evaluate the intervention’s impact on the residents’ malaria prevalence using a cluster-randomized control trial.

**Discussion:**

A policy tool to encourage active malaria prevention and early treatment to residents in Suba South, examined in this trial, may benefit other malaria-endemic counties and be incorporated as part of Kenya’s national malaria elimination strategy.

**Trial registration:**

UMIN000047728. Registered on 29th July 2022.

## Introduction

### Background and rationale {6a}

Since around 2000, the United Nations/Millennium Development Goals (MDGs) and the establishment of the Global Fund have increased funding for global malaria control. There have been significant improvements in the supply side of healthcare services for malaria, including the distribution of long-lasting insecticidal nets (LLINs), the implementation of indoor insecticide spraying (IRS), the use of rapid diagnostic tests (RDT) at community health facilities, and the use of Artemisinin-based Combination Therapy (ACT) in community health facilities. The number of malaria cases and deaths worldwide has decreased significantly to the point where malaria elimination by 2030 was one of the 2015 United Nations Sustainable Development Goals (SDGs) [1, 2]. However, while malaria prevalence in Southeast Asian countries has been shrinking significantly, tropical Africa continues to experience high malaria prevalence [3]. Moreover, the number of deaths and patients worldwide has leveled off, along with the headwind of funding for disease control since around 2015. In addition, many resources have been diverted to the fight against new coronavirus infections, raising the specter of another malaria pandemic. The WHO reports that the pandemic of new coronavirus infections has put the operation of basic health systems, including malaria prevention, diagnosis, and treatment, at risk. The result has been a measured excess of deaths from malaria of about 47,000 people [3]. How to steer and accelerate the fight against malaria in the direction of global elimination once again is one of the most significant global health challenges we face in a post-corona era, and malaria control in tropical Africa is a clear focus of this effort.

This project targets residents of Suba South Sub-County, Homa Bay County, along Lake Victoria in western Kenya, where malaria prevalence remains high. According to the results of a rapid malaria diagnostic test in the census (7060 subjects) conducted by our team (December 2022–February 2023), the positive rate was 16.7%, and even higher for children under 15 years old (24.4%). In the area with the highest infection rate, 69 out of 102 (68%) were positive. Despite the fact that malaria control efforts by national and international aid agencies have been returning to pre-corona pandemic levels, the prevalence rate remains very high in this region.

One of the important factors for the stagnation of the downward trend of malaria infection exists on the demand side, that is, people who use healthcare services for malaria control. The inappropriate and suboptimal uses of LLINs are commonly observed among the residents in the region [4–6]. Thus, it is clear that the top-down intervention, e.g., free mosquito net distribution or IRS program, alone has a limitation in eliminating malaria from the areas. It is necessary to consider measures to encourage preventive actions on the demand side of healthcare. Existing studies suggest that people tend to underinvest in preventive healthcare and spend more on treatment costs of illness [7]. Moreover, people tend to make less effort for preventive healthcare for communicable diseases such as malaria than socially optimal level due to inconsideration of the health of others by ignoring the fact that their own prevention efforts reduce the infection risk of their neighbors [8–10]. We hypothesize that the stagnation of the malaria reduction trend is caused by the fact that residents in malaria-prone areas underestimate the value of preventive healthcare due to the lack of knowledge of benefits from the care and also oversight of direct and indirect costs of illness. In order to address the problem, it is crucial that the residents themselves understand the benefits of malaria prevention and maintain their appropriate use of preventive measures for a long. This project aims to encourage residents to use appropriate malaria prevention methods and seek early treatment continuously through a financial incentive scheme in which a monetary reward is given to those with negative testing results of malaria infection, complemented with malaria education through a tablet-based animated material that we develop.

A financial incentive intervention combined with malaria knowledge education we plan in this study can motivate residents to make further efforts for malaria prevention. Here, we designed a cluster-randomized controlled trial to evaluate its effect on fostering behaviors of malaria prevention and early treatment and reducing malaria prevalence. Thus, we will monitor the behaviors and prevalence of the target residents. The most vulnerable population to malaria is small children, whereas adults are also an important population in malaria transmission since they can act as a reservoir of transmission as asymptomatic infections. At the same time, adults are the ones who decide how they handle malaria prevention and treatments in the family. Thus, the proposed study includes monitoring two target populations: children (zero to 15 years old) and all age groups.

### Objectives {7}

The primary study objective is to evaluate the causal impact of the financial incentive intervention on malaria prevalence in children aged zero to 15 and all age groups during a 6-month follow-up period. The secondary objectives during a 6-month follow-up period are.To measure the impact of the financial incentive intervention on malaria preventive behaviors, especially bed net usage after the 6 months of the intervention,To measure the impact on malaria knowledge of target individuals andTo measure the spillover effects from those exposed to the intervention to their geographic neighbors and those who are socially connected.

### Trial design {8}

The study hires a two-stage randomized controlled trial with 92 clusters with three arms for impact evaluation. In this study, we have two different forms of financial incentive schemes, CCT and LIS, combined with malaria education (EDU), consisting of two intervention arms, while the third arm is for control. We randomly assign these three arms at the cluster level at the first stage.

Clusters are defined as a set of 20 adjacent households based on the household location information obtained in the household census conducted in coastal communities of the Suba South Sub-County from May to July 2021 and include 5968 households. Although there are numerous ways to define 92 clusters with 20 adjacent households from 5968 households in the region, we randomly select a combination of 92 clusters in a way that none of the cluster-comprising households belong to more than one cluster.

Once we define the clusters, they are stratified by the average malaria prevalence and the number of children under 15 years of age in the clusters based on the baseline survey, and one of the three arms is assigned to each of the clusters per stratum based on random numbers generated by a priori on the computer. Figure 1 shows the locations of the clusters on the map and arm types by colors.

**Fig. 1 Fig1:**
[figure not shown]
Map of Suba South showing the locations and the types of arms of the 92 trial clusters

The randomization at the second stage is done at the household level in the two intervention arms, CCT and LIS, to determine which households will receive the treatment within an intervention cluster. It is designed to measure spillover effects within an intervention cluster from the households with treatment to those without treatment. The random assignment at the household level within an intervention cluster is made by asking a household representative to draw a scratch card during a site visit by the survey team for the intervention. The card has a single number from 1 to 10 printed under a seal. If an even number appears on the card drawn, the household will receive the treatment, meaning that (1) the household receives the malaria education (EDU) at the site visit and (2) its household members become eligible for an incentive scheme (CCT or LIS depending on the arm of the cluster). The household will not receive the treatment otherwise.

A power analysis was conducted after taking into account the size of the expected intervention effect, the number of clusters, and the number of households and individuals following a recent examining regression models for a random saturation experiment [11], which fits our two-stage randomization setting. The two intervention arms, CCT and LIS, are randomly assigned to 32 clusters, respectively, while the control arm is assigned to 28 clusters. The cluster-level randomization is supplemented by intra-cluster random assignment at the household level, and the overall structure of the experiment forms a two-stage randomized control trial.

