### Intervention description {11a}

After the baseline survey and blood sampling, the survey team will have site visits to the households in all the target 92 clusters for the intervention. In the control clusters, the survey team will explain the follow-up survey that will be held in 6 months, confirm their continuous participation in the study, and conduct a short interview in the local language, Luo. In the intervention clusters, in addition to the explanation of the follow-up survey and the confirmation of the participation, the survey team will inform that the intervention would be piloted to the household, that the eligibility for the intervention would depend on a number of a scratch card to be drawn by a household representative, that an even number will make the household eligible for the intervention, and that an odd number will make the household ineligible. The survey team will explain the reward scheme of the CCT in the CCT clusters and that of the LIS in the LIS clusters, respectively, and the timing of the follow-up survey (in 6 months). If the household representative, typically the household head or spouse, understands the incentive scheme correctly, he/she will be asked to draw a card from an envelope containing ten cards. If he/she does not understand, the survey team will explain the rule again before he/she draws a card. If an even number is drawn, he/she will be informed that the household receives the treatment, i.e., its members become eligible for the reward scheme and asked to watch the malaria education material on a tablet device that the survey team will bring, and then proceed to a short interview. Otherwise, he/she will be informed that the household does not receive the treatment, and the survey team will conduct a short interview only. Appendix has the instruction script for enumerators in the intervention to be used.

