### Sample size {14}

The malaria RDT positivity among residents in our target area is approximately 30%, based on an independent survey conducted at the same time in our study area. Our census survey suggested an approximate average household size of 5. We aim to detect the expected effect of 30% RDT positivity reduction (to 21%) relative to control both in the direct and spillover effects, with a power of 0.8, a two-sided type-I error of 5%, a cluster size of 20 households, and an intra-cluster correlation coefficient of 0.05. We rely on the optimal saturation [11] and find the required number of clusters is 28 for the control arm and 32 for the treatment arm, where ten households in a treatment cluster end up receiving the treatment, and the remaining ten households are left untreated. We have two intervention arms, each of which to compare to the control arm. Therefore, our total intervention sample consists of 9200 individual subjects from 1840 households grouped into 92 clusters.

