## Statistical methods

### Statistical methods for primary and secondary outcomes {20a}

The intention-to-treat (ITT) analysis is the primary analysis approach for both the primary and secondary outcomes and the per-protocol analysis will be included as a supplementary analysis.

The primary outcome of the study is malaria prevalence by PCR of children aged 0 to 15 6 months after the financial incentive intervention. Based on the PCR examination results, we apply a regression model for two-stage randomized control trial settings, proposed by a study [11], which allows us to identify an unbiased estimate of the ITT and also the spillover effects on treated and untreated households within a cluster while controlling for confounders, including age, gender, house structure, and other socioeconomic status indicators.

For secondary outcomes, the PCR malaria prevalence of all the age groups, the microscopic malaria prevalence, the proportion of participants using the bed net, and the malaria knowledge of the adult participants will be evaluated similarly.

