## Appendix

### The English translation of the intervention script

The following script is used for all the target households:

*We would like to ask all of you who have been cooperating in this research project to continue to join it. As you all know, Homabay County has a very high rate of malaria prevalence. The most effective prevention method is the proper use of insecticide-treated mosquito nets. However, it is not being thoroughly implemented. If we implement appropriate preventive actions, including the use of mosquito nets, and early diagnosis and treatment in health facilities when the infection is suspected, we should be able to contain malaria transmission in the region.*

The following script is used for the households in treatment clusters (CCT and LIS):

*In order to encourage such appropriate preventive actions, this research project will experiment with an educational tool to increase knowledge about malaria and a reward scheme for your efforts to avoid contracting malaria. The reward scheme is to reward those who are confirmed to be malaria-negative at the next survey scheduled in 6 months when the RDT test is conducted. All persons listed under this household in this survey are eligible.*

*Please note that this is an experimental trial with a limited budget; not all households can be eligible for the reward this time. This time, 50% of the households who cooperate with the survey will be eligible for the reward scheme.*

*Whether or not a household is eligible for the reward system will be determined by a scratch card. We will ask a representative of the household to draw a card, and if a card with an even number is picked, the household will be eligible for the reward scheme.*

*If this experiment is successful, we will consider continuing the reward scheme and implementing policies to target more households.*

*If you agree, you will be asked to pick a scratch card. A scratch card has a number from 1 to 10 printed under the seal. You and your family members are eligible for the reward scheme if you draw a card with an even number, i.e., 2, 4, 6, 8, or 10.*

*Please choose who will draw a scratch card?*

[Enumerator Instruction] Ask a respondent to draw a card from the envelope with 10 cards. Once s/he draws a card, remove the seal by a coin in front of them and share the result with them.

The following script is used for the eligible households in CCT clusters:

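### The untreated-versus-control contrast measures announcement and draw effects together with neighbour effects, so it should not be labelled spillover from treated households

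*Protocol article*

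**What the plan says.** Objectives {7} lists, among the secondary objectives, spillover from people exposed to the intervention to their geographic neighbours and social contacts. Trial design {8} gives the purpose of the household draw: "It is designed to measure spillover effects within an intervention cluster from the households with treatment to those without treatment".

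Sample size {14} plans to detect a "30% RDT positivity reduction (to 21%) relative to control both in the direct and spillover effects". The spillover comparison is therefore untreated households against the control arm. The section also says that "ten households in a treatment cluster end up receiving the treatment, and the remaining ten households are left untreated". Statistical methods {20a} will estimate, besides the ITT effect, "the spillover effects on treated and untreated households within a cluster".

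On what households are told, Intervention description {11a} states: "The survey team will explain the reward scheme of the CCT in the CCT clusters and that of the LIS in the LIS clusters". This comes before the card is drawn, and a household with an odd number is then told that it is not treated. The script in the Appendix for all CCT and LIS households mentions the educational tool, the reward for a negative RDT in 6 months, and the 50% eligibility. It adds: "If this experiment is successful, we will consider continuing the reward scheme and implementing policies to target more households".

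Control households receive the general prevention message that goes to everyone, the explanation of the follow-up survey, a request to continue, and a short interview.

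**The concern.** Untreated and control households differ in two respects. The untreated have treated neighbours. They were also told by the survey team that staying negative can earn money, took part in a draw, lost it, and heard that the scheme may later reach more households. The second difference does not come from the treated households.

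Hope of a later reward, or simply knowing that one exists, could raise net use and early treatment. Losing the draw could do the opposite. Explanation for the choice of comparators {6b} describes control and untreated households alike as having neither incentive nor education. That overlooks the announcement and the prospect of extension.

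At stake is what the trial may conclude about spillover, which {14} powers for the same reduction as the direct effect. An announcement effect could be credited to treated neighbours, or disappointment could hide a real neighbour effect. Bed-net use, a secondary outcome analysed in the same way, could respond directly to an announcement.

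**Working it through.** **1. What each group receives ({11a} and Appendix).**

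| Element | Control | Untreated, CCT/LIS | Treated, CCT/LIS |
|---|---|---|---|
| General prevention message | yes | yes | yes |
| Told of reward and possible extension | no | yes | yes |
| Takes part in draw, learns result | no | yes (loses) | yes (wins) |
| Education and eligibility for reward | no | no | yes |
| Treated households in own cluster | no | yes | yes |

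Control and untreated differ in rows 2, 3 and 5. Only row 5 is spillover from treated households. The general message is common to all and does not confound. {11a} has the scheme explained before the draw, while the Appendix gives the amounts to winners only. On either reading, losing households knew that a reward existed.

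**2. The plan's own figures.** Totals: 28 + 32 + 32 = 92 clusters; 92 × 20 = 1840 households; with "Our census survey suggested an approximate average household size of 5", 1840 × 5 = 9200 persons. The stated inputs are "a power of 0.8, a two-sided type-I error of 5%, a cluster size of 20 households, and an intra-cluster correlation coefficient of 0.05".

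Effective sample size is C·m/(1 + (m − 1)·ICC):
- Control: 28 × 100/(1 + 99 × 0.05) = 470.6
- Untreated, one arm: 32 × 50/(1 + 49 × 0.05) = 463.8

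A two-proportion test of 30% against 21% then has power 0.885. Counting households as units (20 and 10 per cluster) gives 0.632. Counting half the persons (50 and 25) gives 0.816. So 28 and 32 clusters at 0.80 do not reproduce exactly. The method cited for the sample size is not shown, so this is not called an error, and nothing below depends on it.

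**3. What the contrast identifies.** Assume additivity: observed difference = neighbour effect + announcement/draw effect. The component values below are assumed; the documents give none.

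| Neighbour | Announcement/draw | Observed | Power |
|---|---|---|---|
| −9 points | 0 | −9 points | 0.885 |
| 0 | −9 points | −9 points | 0.885 |
| −6 points | −3 points | −9 points | 0.885 |
| −3 points | +3 points | 0 | – |

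The first three rows cannot be told apart from this contrast.

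**4. Number of treated households.** With 20 independent draws at 50%, the count is Binomial(20, 0.5). P(exactly 10) = 0.176, P(6 to 14) = 0.959, SD = √(20 × 0.25) = 2.24.

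**5. Could chance variation in that number separate the parts?** Among untreated households, take the regressor as the share of the other 19 households that won. Its SD is √(0.25/19) = 0.1147. The variance of a cluster mean is v = p(1 − p)/m × (1 + (m − 1)·ICC), where m is the number of untreated persons per cluster. The SE for a change in share from 0 to 50% over K clusters is 0.5·√v/(√K × 0.1147). Assumed ranges are m = 25 to 50 and p = 0.21 to 0.30. ICC 0.05 is the protocol's value and 0.15 is an assumed alternative. Power is for 9 points, two-sided 5%.

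| Clusters | ICC | SE, p = 0.21, m = 50 | SE, p = 0.30, m = 25 | Power |
|---|---|---|---|---|
| 64 (pooled) | 0.05 | 0.058 | 0.074 | 0.34 to 0.23 |
| 64 (pooled) | 0.15 | 0.091 | 0.107 | 0.17 to 0.13 |
| 32 (one arm) | 0.05 | 0.082 | 0.105 | 0.19 to 0.14 |
| 32 (one arm) | 0.15 | 0.128 | 0.151 | 0.11 to 0.09 |

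First line as an example: v = 0.1659/50 × 3.45 = 0.01145, √v = 0.107, SE = 0.5 × 0.107/(8 × 0.1147) = 0.058.

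**The case against.** The contrast rests on randomisation and is unbiased for the total effect on an undrawn household in an intervention cluster. That stands. A reader might infer that the estimate is invalid or the allocation compromised, and the documents do not support this. Only the attribution to treated households fails.

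Spillover is a secondary objective. The primary outcome is PCR prevalence in children, and nothing here challenges the treated-versus-control effect of the whole package. That also stands.

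A reader might further infer that the authors will report any difference as reduced transmission. No section commits them to that. {7} includes socially connected people, so information passed on by a treated neighbour is within the objective. But information delivered by the survey team does not come from a treated household, and {8} specifies that source, so the labelling problem remains.

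The Discussion does address losing the draw, but only as a cause of attrition, and it addresses influence between clusters. Neither covers a direct effect of the announcement on behaviour.

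It is tempting to treat the slope on realised share as the true neighbour effect, because every household in these clusters heard the same script. That goes too far. Disappointment may depend on how many neighbours won, which is the regressor itself. The 0-to-50% effect extrapolates linearly from shares mostly between 30% and 70%. Pooling assumes one slope for two schemes, and power is low.

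On the count of ten, {8} and {11a} disclose the individual draws openly, and no loss of power from the variation has been shown.

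**Conclusion.** The point holds as one of labelling and interpretation. What the plan calls spillover from treated to untreated households is the sum of announcement/draw effects and neighbour effects. This follows from the scripts and needs no numerical assumption. The size and sign of the announcement part are unknown, and the splits in the illustration are assumed and additive. It would be wrong to conclude that the estimated difference is itself biased, or that the announcement effect is known to be large.

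The planned data do not separate the parts well. Pooled over 64 clusters, the realised-share slope has an SE of about 0.06 to 0.07 at ICC 0.05 and 0.09 to 0.11 at ICC 0.15, hence power of about 0.13 to 0.34 for 9 points. These figures assume full clusters, independent draws at 50%, 25 to 50 untreated persons per cluster and prevalence of 0.21 to 0.30. The statement that ten households end up treated is a minor wording matter.

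**What to change.** - In {8} and {20a}, name the contrast *effect on undrawn households in intervention clusters (announcement/draw plus neighbour effects)*, and do not attribute it to treated neighbours alone.
- In the limitations, add that untreated households were told of the scheme and its possible extension and lost a draw, whereas control households were not.
- As an exploratory supplement only: among untreated households in the intervention clusters, regress the outcome on the realised share of the other cluster households that drew an even card. Do this by arm and pooled with an arm term, adjusting for strata and number of participating households. State beside it that disappointment may vary with the number of winners, that linearity is assumed, and that precision is low.
- In {14}, say ten treated households on average.

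The cost is some rewording, one extra regression on the recorded draw results, and a more modest spillover claim. No change to conduct or sample size is needed.
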